Building on this existing research, the primary objective of the Family Stress Study is to test the conceptual model (Figure 1), using longitudinal structural equation modeling (SEM), that exposure to chronic stressors is directly associated with higher adiposity among children and partly mediated through alterations in children’s cortisol production and weight-related behaviors. It is hypothesized that (1) chronic stress at baseline will be positively associated with children’s BMI *z* score and waist circumference (WC) at 1- and 2-year follow-up, (2) the association between chronic stress and children’s adiposity outcomes will be partially mediated by children’s cortisol levels and children’s weight-related behaviors, and (3) associations between children’s cortisol levels and weight-related behaviors will be bidirectional (modeled as a cross-lagged structure within the longitudinal design). The secondary objective of this study is to examine the extent to which child sex, caregiver-child relationship quality, caregiver education, and caregiver self-regulation, moderate the associations examined in objective 1. Based on previous research, it is hypothesized that associations between chronic stress, cortisol levels, weight-related behaviors, and adiposity will be stronger among (1) children with less supportive caregiver relationships as compared to those with more supportive relationships [18,19], (2) female children as compared to male children [3,22], (3) children whose caregivers have lower education as compared to children whose caregivers have higher education [23,24], and (4) children whose caregivers have lower self-regulation as compared to children whose parents have higher self-regulation [21].

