### Data Analyses

To summarize baseline caregiver and child characteristics for this paper, descriptive statistics were used. Percentages are presented for categorical data. Means and SDs are used for continuous data.

This study’s objectives will be tested using an SEM approach for longitudinal models that combines latent growth models (LGMs) with auto-regressive and cross-lagged paths using a special parameterization that separates the time-invariant (between-individuals) and time-varying (within-individuals) components [80,81]. Before constructing the SEM models, distributions of all the variables, their skewness and kurtosis levels, and their presence of extreme or outlier responses above or below 3 times the IQR will be explored and outliers will either be removed or Winsorized.

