An incremental model-building approach similar to the recommended approach by Curran et al [80] will be used to test this study’s objectives. The first component in the model-building approach is the LGM of the trajectories across time for the variables’ chronic stressors (explanatory variable), child cortisol and child behavior (mediator variables), and child adiposity (outcome variable). Each variable has its own trajectory and includes an intercept (I), which refers to a baseline value, and a slope (S), which refers to change over time. Of particular importance is that individual child variation in these I and S parameters will be modeled. If any of these components are found to be not statistically significant, they are removed from the model. Typically, the I means and variances are significantly different from 0, but the S means may or may not depict significant linear change. The second component consists of the auto-regressive associations (ie, T2 regressed on T1, and T3 on T2) capturing the rank-order stability of the variables across the 3 time points (eg, the relationship between cortisol at T1 and T2). The third component typically consists of cross-lagged paths or other hypothesized paths between the variables, accounting for growth factors, and stability factors. In this study, this component will consist of the longitudinal mediation paths (ie, from explanatory variable at T1 to mediator at T2, to outcome at T3). The hypothesized model includes 2 partial mediators of the relation between stressors and child adiposity: child cortisol and behaviors. To test mediation, a direct path from stressors at T1 and child adiposity at T3 is also included. A correlational path between the residualized mediators is also included to model any leftover covariance between them. The fourth component will assess the moderation of the mediated paths. For example, to test the hypothesis that the cortisol mediation may differ across the sex of the children, we can use a multiple groups SEM approach that compares the effect size of mediation across male and female children.

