### Conclusions

To design effective obesity prevention interventions, there needs to be a clear understanding of key factors influencing excess weight gain in children. By identifying both the direction and the relative contributions of the biological and behavioral pathways linking chronic stress and adiposity, results from the Family Stress Study will help inform interventions to modify these pathways and reduce obesity risk among young children. Specifically, this research will identify the key behavioral drivers linking stress and obesity to inform which weight-related behaviors should be targeted with interventions in families experiencing high stress. This research will also identify whether the quality of caregiver relationships, child sex, and caregiver education and self-regulation moderate the pathways linking stress and obesity; this information is needed to inform what types of families may be best targeted in obesity prevention interventions. Thus, the results of this research will provide a much-needed basis to inform future childhood obesity prevention interventions.

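### The listed model paths leave hypothesis 3 and the year-1 part of hypothesis 1 without a matching test, contrary to the stated hypotheses and the promised cross-lagged model

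*Protocol article*

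**What the plan says.** The Introduction of the protocol article sets out three primary hypotheses. The first links baseline chronic stress to BMI z score and "waist circumference (WC) at 1- and 2-year follow-up". The third says that associations between cortisol and weight-related behaviors "will be bidirectional (modeled as a cross-lagged structure within the longitudinal design".

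The Data Analyses section opens by promising a model that "combines latent growth models (LGMs) with auto-regressive and cross-lagged paths". The Sample Size Estimation section likewise refers to cross-lagged effects as the target of the power simulation at 300 children.

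Data Analyses then builds the model in steps:
- Growth trajectories come first.
- Next: "The second component consists of the auto-regressive associations (ie, T2 regressed on T1, and T3 on T2".
- The third component is described as typically holding cross-lagged or other hypothesized paths, but for the present cohort the article states that "this component will consist of the longitudinal mediation paths (ie, from explanatory variable at T1 to mediator at T2, to outcome at T3".
- To this, "a direct path from stressors at T1 and child adiposity at T3 is also included".
- Between cortisol and behavior: "A correlational path between the residualized mediators is also included to model any leftover covariance between them".

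The Discussion's Conclusions state what the study will deliver: "By identifying both the direction and the relative contributions of the biological and behavioral pathways". The Abstract and the end of the Introduction say much the same.

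**The concern.** Only one paragraph lists the paths, and it narrows the third component to a single forward chain. Two of the three primary hypotheses need parameters that are not on that list. An analyst who follows it literally has no coefficient to report for hypothesis 3 and none for year-1 adiposity under hypothesis 1. The coefficient labelled direct could also be near zero although stress had already raised adiposity in the first year and the difference persisted. An analyst who instead adds the missing paths once results are in view turns primary tests into post hoc ones.

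**Working it through.** **The plan's own figure.** Sample Size Estimation reports 82% to 86% for all estimated parameters at N = 300, labelled coverage and read as sufficient power. It cannot be reproduced, because no coefficients, variances, alpha or list of simulated paths are given. If it means power at two-sided 5% (assumed), it corresponds to a standardized path of about (1.960 + 0.915)/√300 = 0.166 to (1.960 + 1.080)/√300 = 0.176. The figure is not disputed here. What matters is that the section does not say whether cortisol–behavior lags were among the simulated paths.

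**Hypotheses against listed paths** (T1 = baseline, T2 = year 1, T3 = year 2).

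| Claim | Parameter needed | Listed? |
|---|---|---|
| H1, year 1 | stress T1 → adiposity T2 | No |
| H1, year 2 | stress T1 → adiposity T3, direct and indirect | Direct and mediated, yes; through adiposity T2, no |
| H2 | stress T1 → mediator T2 → adiposity T3 | Yes |
| H3 | cortisol → later behavior and behavior → later cortisol | No; residual correlation only |
| Direction aim | also adiposity → later cortisol or behavior | No |

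**Why the direct path excludes year-1 effects.** Leaving growth factors aside, write

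adiposity T2 = s·adiposity T1 + g·stress T1 + error

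adiposity T3 = s·adiposity T2 + b₁·cortisol T2 + b₂·behavior T2 + d·stress T1 + error

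with a₁ and a₂ for stress T1 → cortisol T2 and behavior T2. The total two-year effect is d + a₁b₁ + a₂b₂ + s·g. The listed paths contain the first three terms and fix g at zero. The coefficient d holds adiposity T2 constant, so an effect confined to the first year gives d = 0.

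**Illustration only.** All coefficients are assumed: s = 0.6; a₁ = a₂ = b₁ = b₂ = 0.15; g = 0.15.
- With d = 0: true total = 0 + 0.0225 + 0.0225 + 0.6 × 0.15 = 0.135. Listed paths give 0.045, and the direct path is 0.
- With d = 0.05: true total = 0.185. Listed paths give 0.095.

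A simulated data set of 2,000,000 records, fitted equation by equation by least squares, returned 0.045 and 0.094, with a direct path of 0.000 in the first case. Adding stress T1 → adiposity T2 recovered 0.150.

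**What the residual correlation shows about H3.** Assume mediator auto-regression of 0.5, correlations of 0.2 among baseline variables, and one cross-lag of 0.2. In the same simulation the residual correlation was 0.001 with cortisol → behavior, 0.000 with behavior → cortisol, and −0.012 with both. The omitted lag appeared instead in an auto-regressive path. The omitted mediator loads on the retained one with weight 0.2 × (1 − 0.2)/(1 − 0.2²) = 0.167, so the auto-regression becomes 0.5 + 0.2 × 0.167 = 0.533. The listed term therefore shows neither the presence nor the direction of a cross-lag.

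**The case against.** The best reply is that the cross-lags are not absent from the article. Hypothesis 3 itself fixes the cross-lagged structure, the opening of Data Analyses repeats it, and the sample size section relies on it. The article condenses a fuller protocol, and the conceptual model figure is not shown. The residual correlation is presented as mopping up leftover covariance, never as the test of hypothesis 3. This stands to the extent that the defect for hypothesis 3 is a contradiction between sections, not a wholesale omission. It does not remove the problem: the one paragraph that enumerates paths says what the component consists of in this study, and the list is worded as complete.

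Second, the growth part of the model lets each child's stress and adiposity have their own intercept and slope, and associations among these could carry some of a first-year effect. That is possible. But the article names no such association as the test of hypothesis 1, and it removes growth components that are not significant.

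Third, the illustration omits those growth factors, and auto-regression among within-child deviations may be well below 0.6. With an assumed 0.33, the missing term would be 0.33 × 0.15 = 0.05 instead of 0.09. This is right, and the figures should carry no weight beyond showing the mechanism.

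Fourth, no path from adiposity back to cortisol or behavior is hypothesized. Its absence leaves no numbered hypothesis untested; it bears only on how broadly the article speaks of direction.

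**Conclusion.** The point holds in a limited form. As listed, the paths contradict the hypotheses and the promised cross-lagged model. Hypothesis 3 and the year-1 part of hypothesis 1 have no matching parameter, and the direct path to year-2 adiposity excludes stress effects already present at year 1. This rests on reading the path list in Data Analyses as complete, which is how it is worded. No numerical size can be derived from the document.

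Three stronger readings are tempting but not supported:
- A reader might infer that hypothesis 1 is untested altogether. Its year-2 part has the direct path and two mediated routes.
- A reader might infer that the study can show no direction at all. The T1, T2, T3 ordering with auto-regression does give temporal order for stress, then mediator, then adiposity. The gap concerns cortisol versus behavior, and adiposity acting back on either.
- A reader might infer that the model discards standing levels of stress because it separates within- from between-child variation. The article models individual intercepts and slopes, so standing levels are represented.

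**What to change.** Before the longitudinal models are fitted, amend the path list in Data Analyses:
- Add cortisol → behavior and behavior → cortisol lags for T1 → T2 and T2 → T3, and name them as the test of hypothesis 3.
- Add stress T1 → adiposity T2.
- Report the total two-year stress effect as the sum of all traced paths, including the one through year-1 adiposity. Alternatively, test hypothesis 1 directly by regressing year-1 and year-2 adiposity on baseline stress, adjusted for baseline adiposity and covariates.
- Either add adiposity → later cortisol and behavior paths, or limit the direction claims in the Abstract, Introduction and Conclusions to the paths tested.
- State which of these paths the N = 300 simulation covered.

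If models have already been run, label the added paths as specified afterwards.

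No new data are needed, since Data Collection says these variables are assessed at all three waves. The cost is a few more parameters in a three-wave model and some precision. Results gives 268 hair samples and 226 valid activity records at baseline. As a rough guide (80% power, two-sided 5%, both assumed, complete records only), the smallest detectable standardized path is 2.80/√300 = 0.162 at 300, 2.80/√268 = 0.171 at 268 and 2.80/√226 = 0.186 at 226, before any attrition. Identification of the enlarged model should be confirmed before it is adopted.

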As with any longitudinal study, attrition is expected. Patterns of missing data and potential bias at time 2 and time 3 will be investigated by comparing demographics and variable scores of participants who are missing to those who are not missing at each time point. In addition to noting and acknowledging any bias due to missingness, the SEM modelling procedure uses a maximum likelihood estimator which also provides one of the best ways to estimate the model parameter estimates in the presence of missing data. While there is no guarantee that the data are missing completely at random, in longitudinal designs, data from earlier time points compensates for the missingness at later time points in the estimation procedure.

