## Results

As illustrated in Figure 3, a total of 571 primary caregivers completed eligibility surveys (Guelph n=298; Hamilton n=273). Of those, 129 did not enroll in this study: 119 did not meet inclusion criteria, 8 declined to participate, and 2 were excluded for incomplete registrations. Of the 442 eligible families enrolled (ie, provided consent), 79 did not complete any baseline measures (ie, did not start this study) and 4 withdrew. Baseline health and behavior surveys were completed for 359 families including 359 primary caregivers (96% women [n=346]), 179 secondary caregivers (92% men [n=166]), and 359 children. Diet recalls were completed for 313 children and 226 children had valid activity monitor wear time (minimum of 360 min for a minimum of 3 days). A total of 301 families completed an at-home health assessment which included anthropometric measures for 301 primary caregivers, 168 secondary caregivers, and 301 children along with the collection of 268 hair samples from the children. Of the 359 families who completed baseline health and behavior surveys, 79% (n=284) identified that they heard about this study through social media, including posts by community organizations that served families and through paid Facebook advertisements.

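### The planned missing-data comparison covers only times 2 and 3, although 13% to 37% of the 359 children already lack a modeled measure at baseline, where no earlier wave exists

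*Protocol article*

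**What the plan says.** The Data Analyses section introduces missing data as expected attrition and fixes the scope of the check: "Patterns of missing data and potential bias at time 2 and time 3 will be investigated". Participants with and without data are to be compared on demographics and variable scores. The words that follow about each time point refer back to those two waves.

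The section then relies on maximum likelihood estimation. It concedes that data may not be missing completely at random, and adds that in longitudinal designs "data from earlier time points compensates for the missingness at later time points in the estimation procedure".

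The Results section reports baseline completeness by measure:
- "Baseline health and behavior surveys were completed for 359 families"
- "anthropometric measures for 301 primary caregivers, 168 secondary caregivers, and 301 children"
- "along with the collection of 268 hair samples from the children"
- "226 children had valid activity monitor wear time"
- "Diet recalls were completed for 313 children"

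In the model-building description, each variable's growth intercept stands for its baseline value, and the autoregressive component regresses time 2 on time 1. Both apply to cortisol, behavior and adiposity.

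**The concern.** The check is aimed at families who drop out later. The article's own counts show that a substantial part of the modeled data is already absent at the first wave. A missing time 1 hair sample or weight has no earlier value behind it, so the sentence on earlier time points gives no support there.

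Anthropometry, hair and monitor wear are all collected by caregivers at home. The exposures include household chaos, caregiver depression and food insecurity, and such conditions could make completion less likely. The article does not show that they do. If they do, or if completion depends on something outside the model that also relates to adiposity or cortisol, then the assumption behind maximum likelihood matters for the intercepts and the time 1 to time 2 paths. Under the stated plan, a report could say that bias from missing data had been investigated without looking at this wave.

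**Working it through.** **Inputs** (Results section): 571 screened, 129 not enrolled, 79 with no baseline measures, 4 withdrawn; children with anthropometry 301, hair 268, valid activity record 226, diet recall 313.

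**The article's own figure.** 571 − 129 = 442 consented; 442 − 79 − 4 = 359. This matches the stated cohort.

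**Baseline missing share** = (359 − observed) / 359. The article gives counts only, so these percentages are derived.

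| Measure | Observed | Missing | Share |
|---|---|---|---|
| Anthropometry | 301 | 58 | 16.2% |
| Hair sample | 268 | 91 | 25.3% |
| Valid activity and sleep | 226 | 133 | 37.0% |
| Diet recall | 313 | 46 | 12.8% |

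**Joint completeness of anthropometry, hair and activity.** The upper bound is the smallest count: 226 / 359 = 63.0%. Hair was collected within the 301 home assessments, so the lower bound is the overlap of hair and activity: 268 + 226 − 359 = 135 (37.6%). If every valid activity record also came from the 301 home assessments, which is an assumption, the lower bound is 268 + 226 − 301 = 193 (53.8%).

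**Where the gaps enter the model.**
- The mediation path runs from stressor at time 1 to mediator at time 2 to adiposity at time 3. The time 1 stressors come from the survey completed for all 359 families, so the home-assessment gaps do not fall on the start of that path.
- Baseline adiposity, cortisol, activity and diet enter through the growth intercepts and the time 1 to time 2 autoregressions. The mediation paths are estimated with those components in the model.
- A child without a time 1 value has at most two of three points for that trajectory. The intercept must then be inferred from later waves and from correlated variables.

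**What a baseline comparison could detect.** With two-sided 5% error and 80% power, the detectable standardized difference between children with and without a measure is (1.96 + 0.8416) × √(1/missing + 1/observed):
- anthropometry, 58 v 301: 0.40
- hair, 91 v 268: 0.34
- activity, 133 v 226: 0.31
- diet, 46 v 313: 2.8016 × √(1/46 + 1/313) = 0.44

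The comparison is therefore informative for moderate differences. A nonsignificant result would not show that small ones are absent.

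**The case against.** The strongest reply is that the estimator already deals with this. Maximum likelihood is not complete-case analysis: a child without baseline hair still contributes the baseline survey and any later data. The article's general statement in favor of maximum likelihood is not tied to a wave. The sentence on earlier time points is also correct as written, since it speaks only of later gaps. All of this stands. A reader might infer that the paths are estimated in a selected, better-functioning subset, but the documents do not support that.

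Other stronger readings also go beyond the text:
- **That this is the largest block of missing data, or is related to exposure.** No figures for times 2 or 3 are given, and nothing links incomplete home assessments to stress.
- **That 37% lack the behavioral mediator.** The figure applies to activity and sleep only. Eating behavior and screen time are caregiver-reported, and 313 children have a diet recall.
- **That hair loss depends on child sex.** The 3 cm is the segment the laboratory analyzes. No minimum length for cutting is stated and no reason is given for the 91 missing samples.
- **That the consented families who never entered the cohort belong to the same problem.** The article says "79 did not complete any baseline measures (ie, did not start this study", and 4 more withdrew: 83 of 442, or 18.8%. That is selection into the cohort, and the content of the eligibility screener is not described.

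It can also be said that such detail belongs in a fuller analysis plan. That would answer a mere omission. Here the article itself names the waves to be checked and leaves out the one for which it reports gaps.

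**Conclusion.** The point holds in a limited form. The stated comparison omits baseline, where 12.8% to 37.0% of children lack a measure that the model uses, and the design-based reassurance does not extend to that wave. The missing-at-random condition on which maximum likelihood depends is therefore unexamined where the article's only missing-data counts lie. Neither the presence nor the direction of bias is established.

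This rests on three assumptions: that the 359 is the analysis cohort; that baseline values are modeled as described, so that incomplete children stay in the likelihood; and that the baseline survey is usable for nearly all families. Some items do have gaps: household income, for example, is not stated for 25 of 359 (7%).

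The estimator need not change. The scope of the check should, because predictors of baseline missingness that are left out of the model can alter the estimates.

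A separate inconsistency deserves correction. Principal Results in the Discussion says that 301 families completed every baseline child measure, which cannot be squared with 268 hair samples and 226 valid activity records.

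**What to change.** - Extend the comparison in Data Analyses to baseline, separately for anthropometry, hair, activity and diet. Compare children with and without each measure on CHAOS, primary-caregiver CES-D, food security, income, education, child sex and age, and site.
- Enter the observed predictors of missingness as auxiliary variables in the maximum likelihood model. Choose them by size of difference as well as by significance, given the detectable differences above.
- State that the sentence on earlier time points does not cover gaps at time 1, and that for those gaps the analysis relies on data being missing at random given the modeled and auxiliary variables.
- Optional: compare the 83 families outside the cohort with the 359 on whatever the screener holds, and add a sensitivity analysis weighted for completion of the home assessment.

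The cost is a few more tables, a slightly larger model and a less favorable statement about missingness. No new data are needed, and the article describes analysis as still under way.

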### Covariates

Primary caregivers report their child’s birth weight, gestational age, duration of breastfeeding, annual and sources of household income, child and caregiver race or ethnicity, and caregiver employment status (full- or part-time). Secondary caregivers report their race or ethnicity and their employment status.

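### The dropout comparison has no stated use beyond acknowledging bias; dropout predictors left outside the SEM should enter the maximum likelihood step as auxiliary variables, with missing at random stated

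*Protocol article*

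**What the plan says.** Under Data Analyses the article expects attrition: "As with any longitudinal study, attrition is expected". The check is worded as follows: "Patterns of missing data and potential bias at time 2 and time 3 will be investigated by comparing demographics and variable scores of participants". The two groups are families with and without data at each of these waves. Its result is given one use: "In addition to noting and acknowledging any bias due to missingness, the SEM modelling procedure uses a maximum likelihood estimator". The reason offered for relying on that estimator is: "While there is no guarantee that the data are missing completely at random, in longitudinal designs, data from earlier time points compensates for the missingness". The gaps meant are those at follow-up.

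The same section describes the model. The growth part covers chronic stressors, "child cortisol and child behavior (mediator variables), and child adiposity (outcome variable"). To this are added autoregressive paths, the mediation chain from T1 stressor through T2 mediator to T3 adiposity, and a direct T1-to-T3 path.

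Demographics appear elsewhere. The Covariates section lists birth weight, gestational age, breastfeeding duration, "annual and sources of household income, child and caregiver race or ethnicity, and caregiver employment status (full- or part-time"). Child sex and caregiver education are planned moderators, along with relationship quality and self-regulation. Recruitment site and marital status are in neither list. No section says how the listed covariates enter the SEM.

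**The concern.** Two things do not fit together. First, the comparison is designed to find what predicts dropout, but no stated step carries a predictor into the estimation. The only stated consequence is a caveat. Second, the justification is incomplete. The article names missing completely at random as the condition it cannot guarantee, but maximum likelihood does not need that condition. It needs missing at random given the variables in the likelihood. Earlier waves of the modelled variables help only as far as they carry the information that drives dropout. They do not fully stand in for a demographic outside the model.

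The article itself makes such a variable plausible. Its Introduction says that low-income and less-educated households have higher stress and carry more of the obesity burden. The mediation chain and the direct path both end at year 2, the last wave and so the one most exposed to cumulative attrition.

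**Working it through.** **Inputs from the article.** No dropout rate, path coefficient or dropout predictor is given, and no stated figure bears on this point, so there is nothing to reproduce. Baseline completeness (Results) shows that part of the compensating information is absent already at T1. Of 359 families:
- 359 - 301 = 58 (16%) lack the child's anthropometry;
- 359 - 268 = 91 (25%) lack a hair sample;
- 359 - 226 = 133 (37%) lack valid activity data.

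**Assumed model** (2,000,000 simulated records; every value is an assumption). D is a demographic, X is stress at T1, M the mediator, Y adiposity, and each e is a separate standard normal error.
- D ~ N(0,1); X = -0.3D + √0.91·e
- Y1 = 0.15X - 0.15D + 0.96e; M1 = 0.2X + 0.98e
- M2 = 0.5M1 + 0.2X + βD + γDX + 0.8e
- Y3 = 0.7Y1 + 0.2M2 + 0.1X + βD + γDX + 0.6e
- logit P(dropout) = m - λD + δX, with m set to give the dropout rate

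X, M1 and Y1 are fully observed. Those who drop out lose both M2 and Y3. Maximum likelihood then factors into M2 given (X, M1, Y1) and Y3 given (M2, X, Y1, M1), each fitted in those who stay. The paths are a (X to M2), b (M2 to Y3) and c' (X to Y3). The Y scale has SD of about 1: √(0.0225 + 0.0225 + 0.0135 + 0.9216) = 0.99 at baseline.

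| β | γ | Dropout | λ | δ | No dropout: a / b / c' / intercept | ML without D | c' change |
|---|---|---|---|---|---|---|---|
| 0 | 0 | 35% | 1.0 | 0 | 0.201 / 0.200 / 0.100 / 0.001 | 0.200 / 0.200 / 0.101 / 0.001 | about 0 |
| -0.1 | 0 | 20% | 0.5 | 0 | 0.227 / 0.214 / 0.124 / 0.000 | 0.226 / 0.213 / 0.123 / -0.008 | -1% |
| -0.1 | 0 | 35% | 1.0 | 0 | 0.227 / 0.214 / 0.124 / 0.000 | 0.223 / 0.213 / 0.120 / -0.026 | -3% |
| -0.3 | 0 | 20% | 0.5 | 0 | 0.281 / 0.311 / 0.152 / 0.000 | 0.279 / 0.308 / 0.150 / -0.023 | -1% |
| -0.3 | 0 | 35% | 1.0 | 0 | 0.282 / 0.311 / 0.151 / 0.000 | 0.271 / 0.297 / 0.144 / -0.071 | -5% |
| -0.3 | 0 | 35% | 1.0 | 0.5 | 0.280 / 0.312 / 0.150 / 0.000 | 0.251 / 0.299 / 0.127 / -0.071 | -15% |
| 0 | -0.1 | 20% | 0.5 | 0 | 0.200 / 0.217 / 0.097 / 0.029 | 0.190 / 0.216 / 0.086 / 0.028 | -11% |
| 0 | -0.1 | 35% | 1.0 | 0 | 0.200 / 0.216 / 0.097 / 0.030 | 0.169 / 0.213 / 0.066 / 0.026 | -32% |

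The -15% row is severe. D keeps a direct effect of half the residual SD of Y3 (0.3/0.6) after baseline adiposity is held fixed. Dropout odds rise by e^1.0 = 2.7 per SD decrease in D and by e^0.5 = 1.6 per unit of stress.

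**A second set of assumptions**, with autoregression 0.7 and 0.5, has dropout depend on both the demographic and stress: logit slopes -0.7 and 0.3 at 30% dropout, or -1.1 and 0.5 at 35%. If the demographic acts on year 2 only through baseline values, the bias is zero. If 30-50% of its effect stays direct, c' moves as follows:
- milder case: 0.124 to 0.120 (-3%) and 0.139 to 0.133 (-4%);
- extreme case: 0.138 to 0.128 (-7%) and 0.166 to 0.148 (-11%).

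The standard error at N=359 is about 0.05, so these shifts are 0.004/0.05 = 0.1 to 0.018/0.05 = 0.4 standard errors.

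**With D as an auxiliary.** In a separate draw with β = -0.3, 35% dropout and λ = 1.0 (δ = 0), the no-dropout values are 0.282 / 0.311 / 0.150 / 0.000. Maximum likelihood without D gives 0.272 / 0.297 / 0.144 / -0.072, and with D as auxiliary 0.283 / 0.310 / 0.150 / 0.000. The additive bias is removed. In a separate draw with γ = -0.1 at 35% dropout, a is 0.199 with no dropout and 0.166 both with and without the auxiliary. A linear auxiliary does not repair bias that comes from effect modification.

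**The case against.** The strongest reply is that the article is a condensed account, and rules for auxiliary variables usually sit in an analysis plan that is not shown. That is fair for thresholds and software detail. It does not cover what the article itself fixes: the one stated use of the comparison, and a justification that omits the condition maximum likelihood needs.

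Three stronger readings are tempting, and the document supports none of them.

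- **That dropout predictors will be kept out of the model.** The article never says so. Income, race or ethnicity and employment are listed as covariates, and child sex and caregiver education are moderators. Any of these may be in the SEM. What can be said is that no stated step enters them.
- **That dropout linked to demographics necessarily biases the year-2 paths.** The variable must be outside the model and still relate to the mediator or outcome given the modelled variables. Otherwise the bias is zero (first row of the table). With additive effects, much of the shift falls on means and intercepts, whereas the hypotheses concern associations.
- **That the plan assumes missing completely at random.** The sentence is a disclaimer, and the clause about earlier time points is informal missing-at-random reasoning.

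Size can also be overstated. A model without baseline adiposity gives -6% (0.248 to 0.232) to -14% (0.318 to 0.273) for the stress path, but the planned model has autoregressive paths, which reduce this.

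One further objection stands. An auxiliary restores the value the model would have given with no dropout. If the demographic is a common cause of stress and adiposity, that value is itself confounded. In the additive simulation c' is 0.150 without D and 0.100 with D as covariate. Such a variable belongs in the model as a covariate, which deals with both problems.

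**Conclusion.** The point holds as a conditional weakness. The plan looks for dropout predictors, states no use for them beyond a caveat, and rests maximum likelihood on an argument that does not cover variables outside the likelihood. If such a variable predicts dropout and relates to year-2 adiposity or a mediator given the modelled variables, year-2 means can be biased and, usually to a smaller degree, the paths as well.

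Under the assumed inputs, with baseline adiposity in the model and additive effects, the stress-to-adiposity path shifts by about 0% to -10%, mostly under 5%. The one severe combination gives -15%. The year-2 intercept shifts by -0.008 to -0.071 in the additive rows with a non-zero direct effect. Shifts of -11% to -32% arise only if the demographic modifies the stress effect. Dropout rate, strength of prediction and residual association are all assumptions. The change is worth making because it is cheap and uses data already collected, although the likely path bias is below one standard error.

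**What to change.** Revise the missing-data paragraph in Data Analyses as follows.

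1. Name missing at random, given the variables in the likelihood, as the working assumption.
2. Say which of the listed covariates enter the SEM and where.
3. Replace the caveat with a rule. Any collected variable that predicts missingness at T2 or T3, or correlates with adiposity or a mediator beyond a set size (for example |r| of at least 0.1), enters the maximum likelihood estimation as an auxiliary variable by saturated correlates, unless it is already in the model as a covariate or moderator.
4. Where such a variable modifies a path, use the interaction or a multiple-group model, because a linear auxiliary does not help there.

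Auxiliaries leave the paths and their interpretation unchanged. The cost is a sentence or two and a few lines of SEM code, with no new data. The article reports that analysis is still ongoing, so the rule can be fixed before the models are run. The downside is added model complexity at N=359, which a cap on the number of auxiliaries would limit.
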